**Follow-up**

The treated area will be observed for approximately 20 minutes after the US-FHR procedure to confirm that there are no changes in the overall condition, including the absence of any adverse events. At the follow-up visit one week after US-FHR, the treated area will again be examined for signs of infection such as redness, warmth, or swelling, and additional treatment or examination will be provided if necessary.

**Data management and statistical analysis**

Sample size calculation

The sample size was calculated using a one-sample t-test to determine whether the mean change in VAS score from baseline differed from zero. Based on a previous study (Fujita N, et al., J Clin Anesth. 2016;31:149–153), the expected mean change in VAS score was set at 20 mm with a standard deviation of 35 mm, yielding a standardized effect size of 0.57. The significance level (alpha) was set at 0.05 (two-tailed), and the target statistical power was 0.8. The calculated sample size was 28 participants. Assuming an approximate 20% dropout rate, the required number of participants was set at 35.

If the actual number of enrolled participants is lower than anticipated, the sample size will be recalculated and may be modified accordingly.

Statistical analysis

Categorical and continuous variables is summarized as numbers (percentages) or medians (IQR), as appropriate. Pain VAS scores, blood flow volumes and surface temperature measures immediately and 1 week after US-FHR were compared with baseline values using the Wilcoxon signed-rank test. P-values were adjusted for multiple comparisons using the Bonferroni correction. Differences in PDI-5-J scores between baseline and the second visit were also assessed using the Wilcoxon signed-rank test. For all analyses, a P-value < 0.05 was considered statistically significant. All analyses were performed using GraphPad Prism (version 10.6.1, GraphPad Software, Boston, MA, USA).

**Quality assurance**

Data analysis

CRFs will be prepared for data analysis. The entries and any corrections on the CRFs will be completed by the investigators. The investigators will complete the CRFs for each participant promptly after each observation and examination. The original CRFs will be stored at [name] Pain Clinic. Any corrections will be made by striking through the original entry with a single line and recording the reason for the correction, the date and time of the correction, and the identity of the person making the correction in the margin. Data analysis will be performed by an investigator who is responsible for data collection but is not involved in performing the fascia hydrorelease procedures.

Discontinuation criteria

The study intervention for an individual participant will be discontinued if any of the following occur during the study period:

1)The participant ceases to attend study visits during the study period.

2)The participant or their legally authorized representative requests withdrawal from the study (withdrawal of consent).

3)It is found that the participant does not meet the inclusion criteria or meets any exclusion criterion.

4)The study as a whole is terminated for any reason.

In addition, the principal investigator or sub-investigators may discontinue the study intervention for a participant at their discretion if any of the following occur:

5) An adverse event occurs that makes continuation of the study difficult or inappropriate.

6) Worsening of complications related to comorbid conditions is observed, making continuation of the study difficult.

7) The participant is judged not to be compliant with the instructions of the treating physician.

8) Any other reason for which the principal investigator or sub-investigators judge that continuation of the study is not feasible.

If none of the events 1)–8) occur and the participant completes the entire study period including the follow-up assessments, participation in the study will be considered complete.

Obligations to report to the ethics committee

The following events will be reported to the ethics committee:

(i) Any amendments to the study protocol.

(ii) Premature termination or completion of the study.

(iii) Any change in the principal investigator.

Study-related documents and data

All records related to the conduct of this study (paper and electronic) will be retained for 5 years after completion of the study. Personally identifiable data will be stored on a stand‑alone computer that is physically isolated from any network and accessible only to the co‑investigator, [name]. At Isesaki Municipal Hospital, the principal investigator, [name], will store the data under the same conditions. Access to the computer containing personal data will be password‑protected and limited to [name], and managed in the same way by [name] at Isesaki Municipal Hospital.

The personal information disclosed to the collaborating institution will be limited to age and medical history; no correspondence table linking these data to direct identifiers will be provided. When providing data containing personal information to the collaborating institution, the data will be sent as a password‑protected Excel file, and the password will be communicated separately.

The data from this study may be used in the future for new research projects that cannot currently be specified. In such cases, a new study protocol will be prepared, reviewed by the ethics committee, and approved by the hospital director. In addition, information about the new study will be posted on the hospital website to ensure that potential participants have the opportunity to opt out of participation.

Protection of personal information and privacy

Direct identifiers such as names and dates of birth will not be removed from the institution. When data are taken outside the institution, chart IDs will be replaced with study participant IDs to anonymize the dataset. A correspondence table linking chart IDs and participant IDs will be created and maintained, and will be stored at [name] Pain Clinic and not taken outside the institution.

Compensation, medical expenses, and support for participants

All drug administration and examinations in this study will be performed within the scope of standard insurance-covered medical care, and no additional fees will be charged for fascia hydrorelease of the arteries. Fascia hydrorelease is considered an extension of clinical procedures already covered by insurance, such as trigger point injections. If any study-related health injury occurs, treatment will be provided using the participant’s regular health insurance in the same manner as for routine clinical care.

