**Study design**

We conducted a prospective, single-arm interventional study to assess the effectiveness of US-FHR in adult patients (aged >20 years) who presented with neck pain to the outpatient departments of [name] Pain Clinic or Isesaki Municipal Hospital between May 1, 2024, and February 28, 2025.

The inclusion criteria were as follows: patients clinically diagnosed with MPS corresponding to chronic primary musculoskeletal pain (MG30.02 according to the International Classification of Diseases, 11th Revision criteria) for nonspecific chronic neck pain, a movement-related pain VAS score of ≥30 mm, and willingness to undergo FHR treatment. Patients were excluded if they: had been diagnosed with conditions that may cause secondary chronic neck pain, such as a history of head or neck trauma, neurological disorders, inflammatory diseases, or tumors; received an additional prescription for analgesics from 1 week before to 1 week after the FHR procedure; could not safely discontinue anticoagulant or antithrombotic therapy, had a bleeding tendency, or showed signs of infection at the planned FHR site; had difficulty in evaluating blood flow in the transverse cervical or dorsal scapular artery using ultrasound; and planned to undergo FHR at other anatomical sites during the study period.

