**Methodology**

Intervention

Patients underwent US-FHR around the target artery during their first visit. Figure 4 illustrates the US-FHR procedure. Patients were positioned in the lateral decubitus position with the treatment site facing upward and the arm placed alongside the torso. US-FHR was performed using a Canon Aplio i700 ultrasound system (authentication number: 228ABBZX00022000) with an i18LX5 probe (frequency range: 4–18.3 MHz; authentication number: 228ABBZX00025000). The probe was placed medial to the acromion to visualize the trapezius and supraspinatus muscles, enabling identification of the artery located between them. The arteries supplying the cervical tissues exhibit considerable anatomical variation; at this site, either the transverse cervical or dorsal scapular artery can be visualized. The artery closest to the pain source and most easily visualized was selected as the target for intervention. After identifying the transverse cervical or dorsal scapular artery that supplies the cervical tissues, arterial blood flow was assessed. US-FHR was then performed at the stacked fascia surrounding the artery. A 27-gauge, 38-mm needle and a 10-mL syringe were used for the injection. Using the out-of-plane technique, the needle tip was visualized around the artery, and 2 mL of normal saline was injected into the stacked fascia around the artery. The artery diameter and blood flow were reassessed at the same location 2 min after performing US-FHR. A video recording of each procedure was made. Patients who were taking analgesics on a regular schedule were instructed to continue their usual medication regimen without interruption or dose modification.

Outcome measurements

The primary outcome was neck pain, measured using the VAS scale during neck movement, assessed 15 min after US-FHR and compared with the baseline value.

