The secondary outcomes were: (1) neck pain VAS score during neck movement, assessed 1 week after US-FHR; (2) pain VAS score at rest, assessed 15 min and 1 week after the procedure; (3) blood flow volume at the FHR-treated site, measured by ultrasound immediately and 1 week after US-FHR; (4) ADL, assessed using the PDI-5-J before and 1 week after US-FHR; and (5) Surface temperature, measured by thermographic camera before, immediately after, and one week after US-FHR. All secondary outcomes were compared with baseline values. Pain VAS scores were determined by measuring the distance (mm) from the “no pain” anchor and the patient’s mark on a 100-mm line, providing a score range of 0–100. Pain at rest and during movement were scored separately. Blood flow in the transverse cervical or dorsal scapular artery was evaluated immediately before and 2 min after US-FHR during the first and second visits. Arterial blood flow at the planned US-FHR site was measured as follows. First, an image of the vessel along its long axis was obtained, and the maximum diameter was recorded. After confirming arterial blood flow using the Superb Microvascular Imaging (SMI) mode, measurements were performed in Pulsed Wave mode. To ensure reliability, the sampling gate was set to two-thirds of the vessel diameter, and the angle correction was maintained below 60°. The blood flow waveform was observed, and the start and end points of one cardiac cycle were visually determined to trace a single heartbeat. Vessel diameters at the measurement site were recorded. To accurately capture the vessel lumen, the SMI flow display was removed, and the image was magnified to enhance clarity. The vessel diameter was measured as the distance between the inner walls of the lumen, and the cross-sectional area was calculated assuming a circular shape. The ultrasound system software then automatically calculated and displayed the corresponding blood flow volumes, which were recorded. At the second visit, blood flow was measured at the same site as during the first visit by reproducing identical imaging conditions. To ensure consistency, images from the previous measurement were printed, and confirmation was made that the trapezius and supraspinatus muscles, and either the transverse cervical or dorsal scapular artery, were visualized in the same manner before proceeding with the measurement. The PDI-5-J, assessed from the first visit (surveyed before US-FHR) to the second visit, was also included as a secondary outcome measure. The PDI-5-J (five-item Japanese version of the Pain Disability Index) is a self-report questionnaire designed to evaluate the degree to which pain interferes with five domains of daily activities: Family/Home Responsibilities, Recreation, Social Activity, Occupation, and Self-Care. Respondents rate their level of disability in each domain on an 11-point scale ranging from 0 (no disability) to 10 (total disability). The total score ranges 0–50, with higher scores indicating a greater degree of pain-related disability. The PDI-5-J was developed by omitting the items on sexual behavior and life-support activities from the original seven-item PDI, reflecting cultural considerations and respondent comfort in Japan. The PDI-5-J has demonstrated good reliability and validity for evaluating pain-related interference with daily activities among Japanese individuals with chronic pain. The painful site was identified, and its surface temperature was measured using a thermographic camera (FLIR C5™, FLIR® Systems, Inc.) before, immediately after, and one week after US-FHR. The use of analgesics was permitted during the study period; however, FHR, trigger point injections using local anesthetics or steroids, and acupuncture therapy were not allowed during the time between the first and second visits.

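### An additional analgesic prescription in the week after the injection is written as an exclusion criterion, so mandatory discontinuation can act as removal of treated patients for a plausible sign of poor response

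*Protocol*

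**What the plan says.** Four statements in the protocol bear on this.

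- **Exclusion (Study design).** Patients are excluded if they "received an additional prescription for analgesics from 1 week before to 1 week after the FHR procedure".
- **Discontinuation (Quality assurance, Discontinuation criteria).** The lead-in to criteria 1 to 4 is mandatory: "The study intervention for an individual participant will be discontinued if any of the following occur during the study period". Criterion 3 reads "It is found that the participant does not meet the inclusion criteria or meets any exclusion criterion". Criteria 5 to 8 are left to the investigators' discretion.
- **Completion (same section).** Participation counts as complete "If none of the events 1)–8) occur and the participant completes the entire study period including the follow-up assessments".
- **Treatment and concomitant care (Methodology).** "Patients underwent US-FHR around the target artery during their first visit". Further FHR is barred before the second visit, in the sentence that ends "acupuncture therapy were not allowed during the time between the first and second visits". That sentence opens with "The use of analgesics was permitted during the study period", and regular users are told to keep their usual regimen unchanged.

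The primary outcome is movement VAS at 15 minutes. Movement VAS, rest VAS, blood flow, PDI-5-J and surface temperature at 1 week are secondary.

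**The concern.** An eligibility criterion should be decidable before treatment. Half of this analgesic window comes after the injection, so whether a patient meets it depends on what happens in the following week. Needing a new analgesic within a week of a pain procedure is plausibly a sign that the procedure did not help.

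Criterion 3 then requires discontinuation. With the single injection already given, site staff have nothing to discontinue except participation, and the completion sentence denies completer status to anyone who triggers it. No sentence says that these patients still have their 1-week outcome assessments.

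There is no comparison group that would lose similar patients, so selective loss would feed directly into the before-after comparison at 1 week. Those comparisons are the study's only evidence that any benefit outlasts the first visit. Data that were never collected cannot be recovered by any later analysis.

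**Working it through.** **1. Reading the rules together.**
- Injection at visit 1; analgesic exclusion open until 1 week later. The second half of the window can be met only after treatment.
- Criterion 3 covers any exclusion criterion and applies throughout the study period, so it reaches that second half.
- Analgesic use is permitted and regular regimens continue. The trigger is therefore an additional prescription, not analgesic use as such.

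**2. The plan's own figure.** The sample size section uses a mean change of 20 mm, SD 35 mm, two-sided 0.05 and power 0.80. An exact one-sample t-test gives 27 patients (power 0.815); the stated 28 gives 0.830. Then 28 / 0.8 = 35, as stated. The point does not rest on this figure; it supplies only n = 35 and SD = 35 mm.

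**3. Shift in the median 1-week change.** Assumptions: 35 injected; normal changes; SD 35 mm, which the protocol does not state for 1 week; k = 1, 2 or 3 removed, since the protocol gives no rate.
- Full-sample median: rank (35 + 1)/2 = 18.
- After removing k patients from below the median: (35 − k + 1)/2 + k = (36 + k)/2, that is rank 18.5, 19 or 19.5.
- Spacing between neighbouring ranks near the median is about SD / [(n + 1) × 0.399] = 35 / (36 × 0.399) = 2.44 mm.
- Shift is about k/2 × 2.44 = 1.2, 2.4 or 3.7 mm. Simulation gives 1.24, 2.47 and 3.72 mm.
- The shift is the same whether the k are the worst responders or a random draw from below the median. If they are drawn at random from all 35, it is 0.

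**4. False-positive chance at 1 week.** True change 0, two-sided Wilcoxon signed-rank test, result in favour of US-FHR, 20,000 simulated samples. The lower figure removes k at random from the below-median half; the upper removes the k worst.

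| Removed | p < 0.05 | p < 0.025 (Bonferroni for two comparisons, assumed) |
|---|---|---|
| 0 | 2.4% | 1.2% |
| 1 | 3.1–5.0% | 1.7–2.9% |
| 2 | 4.1–9.3% | 2.2–5.6% |
| 3 | 5.7–15.4% | 2.9–9.8% |

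**5. Keeping the patients instead.** Suppose added analgesia improves the 1-week score of 3 such patients by an assumed b mm. The reference is the median had they received no added analgesia.

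| b (mm) | Overstatement, 3 drawn at random from below the median | Overstatement, 3 worst |
|---|---|---|
| 10 | 1.2 mm | 0.0 mm |
| 20 | 2.6 mm | 0.0 mm |
| 30 | 3.9 mm | 0.0 mm |
| 40 | 5.0 mm | 0.4 mm |

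Removal overstates the median by 3.7 mm in both columns. Retention is usually less biased, but not always: at b = 30 mm or more in the random case it is slightly worse.

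**The case against.** The strongest reply is that exit from the study is inferred. The rule discontinues the study intervention; it does not cancel the second visit or discard data. The 1-week outcomes and the 1-week site check are set out without an exception for discontinued patients. This stands, which is why the point is that the rule can act as removal, not that the protocol orders it.

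Second, no contact is scheduled between the two visits. Many prescriptions would come to light only at visit 2, where the outcomes can still be measured. This also stands. What then remains is who is analysed, which a statistical analysis plan may settle and which is not raised here.

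Third, the exclusion has a fair purpose. Added analgesia would confound 1-week pain, also in favour of US-FHR, and step 5 shows that keeping these patients is not neutral. This stands and shapes the fix. It does not justify the present wording, which swaps confounding for selection on a post-treatment event.

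A reader might also infer that the discretionary criteria, such as "An adverse event occurs that makes continuation of the study difficult or inappropriate", are an equal source of bias. The protocol shows no link between them and response, and it already plans a 1-week safety check, so they add little. Nor do the documents support a claim of large bias: the higher false-positive rates require exactly the worst responders to be removed and no true effect, and no prescription rate is given.

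**Conclusion.** The point holds in limited form. The protocol makes a post-injection event an exclusion criterion and ties mandatory discontinuation to it, and it does not say that the patients concerned keep their 1-week assessments. Followed as written, this can select treated patients on a plausible sign of poor response and favour US-FHR at 1 week.

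The size is unknown. With 1 to 3 of 35 below-median patients removed and SD 35 mm, the median 1-week change is overstated by about 1 to 4 mm, against a planned change of 20 mm; it is zero if the removed patients respond like the rest. The number removed, normality and the 1-week SD are assumptions.

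A reader might extend this to the main result. The documents do not support that: the primary outcome is measured 15 minutes after the injection, before almost any such prescription, and would be affected only if these patients were dropped from the analysis altogether. The wording should be corrected, but the primary conclusion does not depend on it.

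**What to change.** - **Study design:** end the analgesic exclusion at the injection.
- **Discontinuation criteria:** state that criterion 3 stops treatment only before the injection, and that every injected patient who has not withdrawn consent keeps the planned 1-week outcome and safety assessments.
- **CRF:** record any later additional prescription, with drug and date.
- **Reporting:** give the 1-week results for all injected patients and again without those given added analgesia, with their number. State that added analgesia may itself improve the scores, so neither result alone is unbiased.
- **Patients already injected:** retain and report any 1-week data collected. The protocol gives both February 2025 and March 2026 as the end of recruitment, so some changes may come too late to apply prospectively.

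The cost is wording in two sections, one CRF item and a second set of 1-week results. No visit is added, because the 1-week visit is already planned.

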**Expected outcomes of the study**

If this study scientifically demonstrates that pain can be treated by US-FHR around blood vessels, it will provide a new therapeutic option for pain management.

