**Research protocol: part 1**

**Project summary**

This study investigates the therapeutic potential of ultrasound-guided fascia hydrorelease (US-FHR) around cervical arteries for patients with cervical myofascial pain syndrome (MPS). Adults aged 20 years or older with cervical pain diagnosed as MPS and reporting movement-evoked pain of at least 30 mm on the visual analog scale (VAS) will be enrolled. The intervention targets the transverse cervical or dorsal scapular artery, which supply the trapezius, levator scapulae, and related cervical soft tissues. Under real-time ultrasound guidance, saline will be injected into the periarterial fascial planes to release adhesions and potentially improve local blood flow and tissue mobility.

The primary objective is to determine whether periarterial US-FHR produces clinically meaningful reductions in cervical pain intensity, assessed by VAS at rest and during neck movement at baseline and follow-up. Secondary objectives include evaluating changes in arterial blood flow using Doppler ultrasound and assessing improvements in activities of daily living (ADL) with validated disability questionnaires. Safety will be monitored by recording adverse events related to the injection procedure, including bleeding, hematoma, and infection. By integrating subjective pain outcomes, objective hemodynamic measurements, and functional indices, this study aims to clarify whether ultrasound-guided periarterial fascia hydrorelease can serve as a safe and effective treatment option for patients with cervical MPS and significant movement-evoked pain.

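### The protocol sets a causal objective and expects a causal conclusion, but a single-arm, open comparison of VAS with zero change cannot attribute the fall in pain to US-FHR.

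*Protocol*

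**What the plan says.** **Design.** Protocol, Study design: "We conducted a prospective, single-arm interventional study to assess the effectiveness of US-FHR". The protocol describes no concurrent control, sham, participant blinding or external benchmark.

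**Selection.** The same section requires "a movement-related pain VAS score of ≥30 mm" for entry. Movement VAS is also the primary outcome, read 15 minutes after the procedure and compared with baseline.

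**Timing.** Protocol, Methodology: "Patients underwent US-FHR around the target artery during their first visit". No run-in or repeat baseline is described.

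**Null hypothesis.** Protocol, Data management and statistical analysis: the sample size rests on a one-sample t-test "to determine whether the mean change in VAS score from baseline differed from zero". The planned analysis compares post-procedure values with baseline by the Wilcoxon signed-rank test, with Bonferroni adjustment.

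**Objective and intended conclusion.** The Project summary states the primary objective causally, as whether periarterial US-FHR produces a clinically meaningful fall in pain. It also aims to clarify whether the procedure "can serve as a safe and effective treatment option for patients with cervical MPS". The Expected outcomes section continues in the same vein: "If this study scientifically demonstrates that pain can be treated by US-FHR around blood vessels", then a new therapeutic option follows.

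**The concern.** The hypothesis tested and the conclusion sought are different things. Zero is the right reference for a treatment effect only if pain marks would not move without the specific action of the saline release. In an open study of a needle procedure, the patient knows that treatment has been given and marks the scale a quarter of an hour later. Expectation, attention and the needling itself can all lower the mark. If the qualifying VAS is also the baseline, selection at 30 mm adds some regression to the mean. The design cannot separate any of these from US-FHR.

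At stake is what a significant P-value will be taken to mean. Under the present wording it would be read as evidence of efficacy. The Problems anticipated section mentions only recruitment, and neither placebo response nor regression to the mean is mentioned anywhere. The protocol does not call itself a pilot or exploratory study. It also asks for a clinically meaningful reduction without naming a minimum change to beat.

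**Working it through.** **1. The plan's own figure.** Inputs from the sample size section: mean change 20 mm, SD 35 mm, two-sided alpha 0.05, power 0.80. Then d = 20/35 = 0.571. By the noncentral t distribution, power is 0.7996 at n = 26, 0.815 at n = 27 and 0.830 at n = 28. The minimum is 27 against the stated 28, and 28/0.8 = 35. The arithmetic is sound; the problem lies in the inference.

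**2. What rejects zero.** The critical mean change is t(0.975, n−1) × SD/√n.
- n = 28: 2.052 × 35/√28 = 13.6 mm
- n = 35: 2.032 × 35/√35 = 12.0 mm

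At SD 35 mm, an observed mean fall of that size is significant whatever caused it.

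**3. Rejection rate with no specific effect.** Set the specific effect to zero and let a non-specific fall of m mm remain. The rate is the noncentral t power at d = m/35. The values of m are assumptions, because the documents give none.

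| Assumed fall m | n = 28 | n = 35 |
|---|---|---|
| 0 mm | 5% | 5% |
| 5 mm | 11% | 13% |
| 10 mm | 31% | 38% |
| 15 mm | 59% | 69% |
| 20 mm | 83% | 91% |

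If the SD of change were 25 mm (assumed), the rates at n = 28 for 5, 10 and 15 mm would be 18%, 53% and 86%. These are t-test rates at an unadjusted 0.05. A Bonferroni adjustment lowers them: at alpha 0.025 the 20 mm row becomes 74% and 84%. It does not change what the test compares.

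**4. Regression to the mean alone.** Assume that the qualifying mark is the baseline and that VAS is normal before selection. Then

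RTM = (1 − ICC) × SD × φ(z)/(1 − Φ(z)), with z = (30 − mean)/SD.

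Assumed ranges: population mean 35–55 mm, SD 20–25 mm, ICC 0.6–0.9.
- Largest: mean 35, SD 25, ICC 0.6. z = −0.20, ratio 0.675, RTM = 0.4 × 25 × 0.675 = 6.8 mm.
- Smallest: mean 55, SD 20, ICC 0.9. z = −1.25, ratio 0.204, RTM = 0.1 × 20 × 0.204 = 0.4 mm.
- At ICC 0.9 throughout: 0.4 to 1.7 mm.

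At SD 35 mm, a shift of 0.4 to 6.8 mm is significant 5% to 17% of the time at n = 28 and 5% to 20% at n = 35. At 1.7 mm the rate is about 6% for either n.

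**5. Safety.** If no adverse event were seen in 35 patients, the exact two-sided 95% upper limit would be 1 − 0.025^(1/35) = 10.0%.

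**The case against.** The strongest reply is that an openly declared single-arm study is a legitimate first step for an effect that, by the Rationale section, has not yet been scientifically evaluated, and that the missing control is its known limit. That stands, and this point does not ask for a control arm. It does not rescue the wording: objective and intended conclusion belong to the protocol, and both are causal.

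A second reply is that the Expected outcomes sentence is conditional, and that the Project summary only aims to clarify whether the procedure can be an option. This is fair, and the protocol should not be said to have decided the result in advance. But the condition presumes that this design could demonstrate treatment, and the primary objective is causal without any condition.

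Third, regression to the mean is probably the lesser mechanism. Fifteen minutes leaves little room for day-to-day fluctuation to regress, which points to the high-ICC end. The protocol does not say that the qualifying mark is the baseline, and the patient flowchart is not shown, so a separate baseline cannot be excluded. This stands too.

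A reader might infer that a significant result is likely even if US-FHR does nothing specific. The documents do not support that. At the protocol's SD, the rate passes 50% only with an assumed non-specific fall of about 15 mm, and no size for such a response is given.

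Finally, the analyst does not perform the procedure (Quality assurance section). That does not help here, because the outcome is the patient's own unblinded mark.

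**Conclusion.** The point holds as a mismatch between design and claim. A test against zero in one open arm can show that VAS fell after US-FHR, but not that US-FHR caused the fall. This follows from the text alone and does not depend on the size of the non-specific response.

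The size is uncertain. At SD 35 mm, assumed non-specific falls of 5 to 15 mm raise the chance of a significant result from 5% to between 11% and 59% (n = 28) or between 13% and 69% (n = 35). Regression to the mean contributes 0.4 to 6.8 mm under assumed inputs, probably near the lower end at 15 minutes. Placebo, needling and expectation are likely the larger part.

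On safety, the protocol records adverse events but sets no criterion. With 35 patients, even an event-free study would leave a rate of up to 10.0% compatible with the data, which is too wide to conclude that the procedure is safe.

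**What to change.** **Essential.** Reword the primary objective in the Project summary and the Expected outcomes section. They should say that the study estimates the change from baseline after US-FHR without a control, cannot attribute that change to the procedure, and informs a controlled trial. Name placebo and needling response and regression to the mean as limitations. In place of a conclusion that the procedure is safe, report the observed adverse-event rate with an exact 95% CI. This can be done even if enrolment has ended.

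**Optional, for participants still to be enrolled.** Use one VAS mark for eligibility and a second, taken just before the procedure, as the analysis baseline. This reduces regression to the mean but leaves placebo response untouched. It may no longer be possible for some or all participants: the Study design section describes presentation up to February 2025 in the past tense, while the Duration section runs recruitment to March 2026.

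**Cost.** A more modest claim, and one extra VAS line per participant if the optional step is taken, with perhaps a slightly smaller estimated change.
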